## Abstract

**Introduction:**

Chronic non-specific low back pain (CNLBP) represents the most commonly encountered subtype of low back pain (LBP) in clinical practice. It has no clearly identified etiological factors and is prone to recurrence, which severely compromises patients’ quality of life. Moxibustion therapy is commonly utilized in China for managing chronic pain conditions and has demonstrated favorable clinical outcomes. However, high-quality randomized controlled trials remain scarce, and the mechanism of action of moxibustion remains unclear. This severely restricts the credibility of moxibustion therapy and its global promotion and application. Consequently, the present research aims to conduct a comprehensive evaluation of the therapeutic efficacy of moxibustion for the management of CNLBP. Additionally, this study will employ modern scientific techniques to conduct a preliminary investigation into the mechanism of action of moxibustion.

**Methods and analysis:**

This study will be conducted simultaneously across three tertiary hospitals in China. 150 participants diagnosed with CNLBP will be recruited for this study. Subsequently, these participants will be randomly assigned, following a 1:1 allocation ratio, to undergo either moxibustion or sham moxibustion intervention in accordance with the established research protocol. Treatment will be administered at an identical set of acupoints for all participants: bilateral BL23 (Shenshu), GV3 (Yaoyangguan), and GV8 (Jinsuo). Each session will last 30 min, administered three times weekly for 8 weeks, and an 8-week follow-up will be conducted after the completion of the moxibustion intervention. Change in Numerical Rating Scale (NRS) scores from baseline to the 8-week post-intervention assessment constitutes the primary outcome measure. Secondary outcomes will include assessments via the Oswestry Disability Index (ODI), Fear-Avoidance Beliefs Questionnaire (FABQ), 36-Item Short Form Health Survey (SF-36), Global Perceived Effect (GPE), and functional near-infrared spectroscopy (fNIRS). Evaluations for this research will be conducted at baseline, following the intervention (the fourth week), after the completion of intervention (the eighth week), and during the follow-up period (week 16).

**Discussion:**

The results obtained from this research are expected to indicate that moxibustion therapy can function as a highly efficacious treatment approach for managing CNLBP. Additionally, this trial will employ fNIRS technology to investigate the activation characteristics of pain-related cortical regions in the brains of CNLBP patients before and after moxibustion treatment. This will contribute to elucidating the underlying mechanisms of moxibustion.

## 1 Introduction

Low back pain (LBP), a highly common clinical condition, adversely affects patients’ work performance and social activities, imposing a substantial socioeconomic burden (1). Epidemiological research consistently shows that nearly 80% of adults have at least one LBP episode in their lifetime (2). Additionally, 22%–65% of patients report recurrence at least once a year (3). Chronic non-specific low back pain (CNLBP) is the most common subtype, accounting for 80%–90% of all LBP cases (4). It manifests as pain or discomfort between the costal margin and gluteal fold, lasting over 12 weeks with no clearly identifiable cause.

The pathogenesis of CNLBP is highly complex and has not been fully elucidated. Recent research indicates that it is associated with a dynamic interplay among biological, psychological, and social factors (5). Pharmacological interventions are no longer the primary therapeutic choice for CNLBP management due to their limited efficacy, unpredictable adverse effects, and potential risk of dependency (6, 7). Invasive therapies including epidural glucocorticoid injections and surgical procedures entail high costs and may confer greater risks of adverse events compared to non-invasive alternatives, without guaranteed resolution of patient suffering, resulting in their rare clinical adoption (8, 9). At present, clinical guidelines indicate that non-pharmacological interventions should be the first choice for effective management of chronic LBP (10). However, conservative approaches such as motor control exercises and cognitive functional therapy generally demonstrate only small effect sizes (11, 12). Consequently, it remains imperative to explore novel complementary therapies to address these clinical challenges (13). Moxibustion, as a classical traditional Chinese medicine (TCM) modality widely employed for chronic pain management, shows promise as an effective strategy for managing CNLBP.

Moxibustion is frequently combined with acupuncture in clinical practice. Moreover, it can effectively address the issue that some patients fear pain caused by invasive acupuncture, thereby reducing their anxiety toward treatment. In recent years, moxibustion has been widely adopted in China’s healthcare system. According to previous studies, its therapeutic effects primarily derive from two mechanisms: the physiological responses to heat stimulation generated through combustion of moxa (14, 15), and the chemical stimulation from pharmacological components within the herb (16). This perspective characterizes the TCM paradigm of health and disease, highlighting the crucial role of endogenous regulatory processes in maintaining homeostasis amidst external perturbations. In China, moxibustion has been extensively applied for managing various pain-related disorders including arthritis (17), dysmenorrhea (18), postherpetic neuralgia (19) and musculoskeletal pain syndromes (20), with documented beneficial clinical outcomes. Based on these experimental results, after moxibustion intervention, the patients’ pain symptoms were alleviated, demonstrating the potential clinical application of moxibustion. Furthermore, clinical observations and self-reported outcomes suggest that moxibustion may improve both physiological and psychological wellbeing, which aligns with its widespread adoption as a preventive healthcare modality in Chinese populations. Nevertheless, high-quality clinical research investigating moxibustion for CNLBP remains scarce, and its therapeutic efficacy and safety profile require further validation through rigorously designed studies.

## 2 Methods

### 2.1 Trial design

This is a multicenter, single - blind, randomized controlled trial in which 150 eligible participants will undergo 1:1 randomization to receive either verum moxibustion therapy or a sham control procedure. This study will span a total duration of 16 weeks, comprising an 8-week therapeutic intervention phase followed by an 8-week follow-up period.

This trial has been registered on the International Traditional Medicine Clinical Trial Registry (ITMCTR2025001296). This study protocol adheres to the SPIRIT reporting guidelines (21). The SPIRIT checklist of this trial is given in Supplementary material. The flow diagram of this trial is illustrated in Figure 1, while the comprehensive schedule for the study is outlined in Table 1.

**FIGURE 1 F1:**
[figure not shown]
Trial flow diagram.

**TABLE 1 T1:** Trial schedule.

	Study period			
	Inclusion	Treatment		Follow-up
Assessment	Baseline	Second	Third	Fourth
Measure point (after inclusion)	0 week	4 weeks	8 weeks	16 weeks
Inclusion criteria	✓			
Exclusion criteria	✓			
Informed consent	✓			
Randomization and allocation	✓			
Intervention		1–8 week		
NRS	✓	✓	✓	✓
ODI	✓	✓	✓	✓
FABQ	✓	✓	✓	✓
SF-36	✓	✓	✓	✓
GPE			✓	
fNIRS	✓		✓	
Adverse events	Any time during the intervention and follow-up			

✓, required; NRS, Numerical Rating Scale; ODI, Oswestry Disability Index; FABQ, Fear Avoidance Beliefs Questionnaire; SF-36, 36-Item Short Form Health Survey; GPE, Global Perceived Effect.

### 2.2 Recruitment

This study will be conducted simultaneously across three tertiary hospitals in China. Patient recruitment will be implemented through a multimodal strategy incorporating social media platforms (WeChat), local newspaper advertisements, and posters displayed in community service centers to ensure adequate participant enrollment.

### 2.3 Eligibility criteria

#### 2.3.1 Inclusion criteria

(1) Meet the diagnostic criteria for CNLBP (4);

(2) Aged between 20 and 55 years (inclusive);

(3) Score ≥ 3 on the NRS;

(4) Sign the informed consent form formulated specifically for this study.

#### 2.3.2 Exclusion criteria

(1) Misdiagnosis;

(2) LBP associated with radiculopathy or nerve root injury;

(3) History of spondylolisthesis or lumbar spine surgery;

(4) LBP resulting from acute severe lumbar muscle tears or strains;

(5) LBP secondary to visceral organ pathologies, including nephrolithiasis, urinary tract infections, gynecological disorders, and malignant tumors;

(6) Concomitant severe systemic diseases such as uncontrolled hypertension or hematological disorders, or psychiatric disorders such as major depressive disorder or schizophrenia;

(7) Pregnant or lactating women;

(8) Presence of skin ulceration or infection at the treatment site;

(9) History of allergy to moxibustion or its components;

(10) Individuals who have received relevant treatments such as medications, physical therapy, or invasive procedures within the past 3 months, which could confound the study outcomes.

#### 2.3.3 Suspension criteria

(1) Patients who refuse to continue participation for personal reasons during the trial;

(2) Occurrence of serious adverse events (SAEs) directly attributable to the intervention, including skin burns, syncope, or other life-threatening complications;

(3) Participants demonstrating non-compliance with the study protocol, such as unscheduled treatment modifications or concurrent use of prohibited therapies.

### 2.4 Randomization

The study will employ a permuted block randomization method (with block size set to 4) stratified by research center for sequential allocation of participants. The randomization sequence will be generated by a statistician independent of the study team using SAS software (version 9.4; SAS Institute Inc., Cary, NC, USA). Research personnel will have no access to the randomization sequence. Randomization numbers will be sealed in sequentially numbered opaque envelopes and stored in a double-locked cabinet. Following completion of baseline assessments and submission of informed consent forms, envelopes will be opened in sequential order of enrollment to reveal group assignments. The allocation sequence will remain concealed such that the next participant’s assignment cannot be predicted in advance.

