### 2.5 Blinding

Throughout the trial, the subjects will remain blinded to their group assignments. Specifically, each subject will be assigned to a separate treatment room to prevent participant-to-participant communication. Due to the unique characteristics of moxibustion therapy, it is difficult to implement blinding among the treating physicians. However, the data collectors, outcome assessors, and statisticians will be blinded to the details of treatment allocation and group assignments throughout the trial. Moreover, they will not be permitted to share any research-related information with each other. This approach will enhance the reliability of the study results. Unblinding will occur only in the event of serious adverse events or after study completion and final data analysis.

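### A single disclosed block size of 4 within centre, with unblinded treating physicians, does not deliver the unpredictability that section 2.4 asserts: up to one third of allocations could be deduced by a fully informed observer

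*Protocol article*

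**What the plan says.** Section 2.4 specifies a "permuted block randomization method (with block size set to 4) stratified by research center". An independent statistician generates the sequence, and research personnel have no access to it. Randomization numbers sit in sequentially numbered opaque sealed envelopes in a double-locked cabinet. After consent and baseline assessment, "envelopes will be opened in sequential order of enrollment to reveal group assignments". The section closes by saying, without qualification, that the next participant's "assignment cannot be predicted in advance".

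Section 2.5 concedes that "it is difficult to implement blinding among the treating physicians", while data collectors, outcome assessors and statisticians stay blinded. Sections 2.6.1 and 2.6.2 give the arms different working distances and put an insulating membrane in the sham holder, so whoever delivers a session can tell which arm it is.

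The design is 1:1 with 150 participants (section 2.1) at three hospitals (section 2.2). The article does not say who enrols, who opens the envelopes, or how many practitioners treat at each centre.

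**The concern.** Concealing the list and being unable to predict from it are different properties. Envelopes hide the next code from someone who knows nothing of the earlier codes. They give no protection against someone who has counted the earlier ones and knows that every run of four at the centre holds two of each arm. The fourth allocation of a block is then always known, and the third is known whenever the first two match. The treating physicians as a group hold the centre's allocation history, and the article supplies the block size.

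What is at stake is selection at entry. If someone who can predict also influences who is enrolled and when, patients expected to do well could be steered towards one arm. The primary outcome is a participant-rated pain score (section 2.7.1). The Discussion offers independent outcome assessment as the answer to unblinded practitioners, but that does not act on selection. The baseline covariate in the section 2.11 model would remove only the part of such selection that works through baseline pain.

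**Working it through.** The article gives no figure for predictability, so there is none to reproduce; it makes only the absolute statement.

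**Inputs from the article:** block size 4, stratified by centre (section 2.4); 1:1 ratio and 150 participants (section 2.1); three centres (section 2.2).

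**Assumptions:** the observer knows the block size and the order of enrolment; where a per-centre count is needed, 50 per centre; where knowledge is partial, each earlier assignment is known independently with probability *f*.

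**1. Full knowledge of the centre's history.** A block of two A and two B has 4!/(2!·2!) = 6 equally likely orders.

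| Position in block | P(known with certainty) | P(best guess correct) |
|---|---|---|
| 1 | 0 | 1/2 |
| 2 | 0 | 2/3 |
| 3 | 1/3 (first two match) | 1/3·1 + 2/3·1/2 = 2/3 |
| 4 | 1 | 1 |
| Sum | 1.333 | 2.833 |

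- Certain: 1.333/4 = 33.3%.
- Best guess correct: 2.833/4 = 70.8%, against 50% by chance.
- Count: 150/3 = 50. With 50 per centre there are 12 full blocks and a part-block of 2, in which nothing is certain: 3 × 12 × 1.333 = 48.

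**2. Partial knowledge.** Position 3 is certain if the first two match and both are known: *f*²/3. Before position 4, one arm has already been used twice; the position is certain if both of those assignments are known: *f*². The certain share is therefore (*f*²/3 + *f*²)/4 = *f*²/3.

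| Share of earlier assignments known | Certain allocations |
|---|---|
| 100% | 33.3% |
| 75% | 18.8% |
| 50% | 8.3% |
| one third | 3.7% |

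Simulation of the same set-up agrees with these values.

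**3. Randomly varying block sizes.** This was simulated for centres of 50 (1,500 replicates). The observer knows the full history and the set of possible sizes, but not the size of the current block.

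| Scheme | Certain | Best guess correct |
|---|---|---|
| Fixed 4 | 32.1% | 70.2% |
| Random 4 or 6 | 5.4% | 69.0% |
| Random 4, 6 or 8 | 2.3% | 67.8% |

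The fixed-4 row sits slightly below the exact values because of the part-block at the end (48/150 = 32%). Varying the size removes most of the certainty and little of the general guessability.

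**The case against.** The strongest reply has four parts.

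- **One third is a ceiling.** It belongs to an observer who knows the block size, the enrolment order and every earlier assignment at the centre. Section 2.5 says only that blinding the treating physicians is difficult. It does not say that any one of them treats, or hears about, every patient. A reader might infer that a third of this trial's allocations are in fact known in advance; the article does not support that. This stands, and is why the figure is given as an upper bound with a range.
- **The route to bias is not shown.** A reader might also infer that site staff can steer enrolment. That requires the person who can predict to be, or to inform, the person who screens or enrols. The article does not say whether these roles are separate, and an article may leave this to the full protocol. This stands too: the silence is not an error, and the harm is conditional.
- **The safeguards are real.** The independent statistician, opaque sealed envelopes, locked cabinet and denied access are sound, and the closing sentence could be read as a statement about list concealment only. This stands in part. These measures protect the list, but the sentence speaks of prediction, which they do not prevent.
- **The remedy moves the guess rate little.** From 70.8% to about 68% is a small gain, and someone inclined to steer can act on a good guess. This stands. The gain lies in removing certainty, so varying the blocks is not enough by itself.

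It would also be too strong to say that nothing in the analysis could help, since baseline adjustment deals with selection acting through baseline pain.

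**Conclusion.** Wrong as written. The absolute claim in section 2.4 describes a property that a disclosed, fixed block of 4 within centre cannot have when the treating physicians know the assignments they deliver. Even an observer with half the history would know about 8% of allocations for certain.

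The bound of 33.3% certain and 70.8% guessed correctly is exact for 1:1 blocks of 4 under full knowledge. The lower figures rest on the assumed shares of earlier assignments known, and the count of 48 on an assumed 50 per centre. The article does not show that selection bias will occur, and that is not claimed here. The defect is an avoidable weakness in the design together with a sentence that overstates its protection.

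**What to change.** - Have the independent statistician generate new centre-stratified lists with randomly varying block sizes (for example 4, 6 and 8), with the sizes not disclosed to the sites. If recruitment has begun, apply them to all remaining allocations; the published size of 4 then no longer describes the lists in use.
- Replace the absolute sentence in section 2.4 with one that says what the procedure does: the list is concealed until each envelope is opened, and varying undisclosed block sizes limit prediction from earlier assignments.
- Because best guesses would still be right about 68% of the time, ensure that those who screen and enrol are not told earlier assignments. If the full protocol already provides for this, one sentence in the article is enough.

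**Cost.** New lists from the same SAS software and new envelopes. The possible end-of-list imbalance rises from 2 to 4 per centre (half the largest block). If all three centres fell the same way, the split would be 81 to 69. Comparing 81 × 69/150 = 37.26 with 75 × 75/150 = 37.50 gives a loss of information of about 0.6%. A change in mid-recruitment could leave one unfinished block of 4 per centre, adding at most 2 more to the imbalance there.

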### 2.5 Blinding

Throughout the trial, the subjects will remain blinded to their group assignments. Specifically, each subject will be assigned to a separate treatment room to prevent participant-to-participant communication. Due to the unique characteristics of moxibustion therapy, it is difficult to implement blinding among the treating physicians. However, the data collectors, outcome assessors, and statisticians will be blinded to the details of treatment allocation and group assignments throughout the trial. Moreover, they will not be permitted to share any research-related information with each other. This approach will enhance the reliability of the study results. Unblinding will occur only in the event of serious adverse events or after study completion and final data analysis.

### 2.6 Interventions

#### 2.6.1 Moxibustion group

All practitioners in this trial must hold a qualified license in traditional Chinese medicine (TCM) and possess a minimum of 3 years of work experience. Moxibustion intervention will be carried out at the following acupoints: bilateral BL23 (Shenshu), GV3 (Yaoyangguan), and GV8 (Jinsuo) acupoints (Figure 2). After igniting one end of a moxa stick and securing it with a supporting device, the burning end will be positioned 3–5 cm above the designated acupoints, aiming to maintain the local skin temperature at 43 ± 1 °C. Participants will experience warmth without a burning sensation. Each moxibustion session will last 30 min, be administered three times per week, and continue for 8 weeks.

**FIGURE 2 F2:**
[figure not shown]
Location of acupoints. BL23 (Shenshu); under the spinous process of the second lumbar vertebra, 1.5 cun lateral to the posterior midline. GV3 (Yaoyangguan); on the posterior midline, under the spinous process of the fourth lumbar vertebra. GV8 (Jinsuo); on the posterior midline, under the spinous process of the ninth thoracic vertebra.

#### 2.6.2 Sham moxibustion group

Participants will undergo sham procedures at acupoints identical to those used for the true moxibustion group. After igniting and securing the moxa stick, the burning end will be placed 8–10 cm above the designated acupoints to maintain the local skin temperature at 37 ± 1 °C. To prevent thermal and smoke radiation from penetrating the skin, a heat-insulating metal membrane will be integrated into the base of the moxa stick holder. This modification has been proven in multiple previous studies to effectively block heat and smoke transmission (22–24). The moxa stick holder will have an identical appearance to that used in the moxibustion group. Participants will detect the aroma of burning moxa but will not experience thermal stimulation. The treatment duration and course will be consistent with those in the moxibustion group.

### 2.7 Outcome measures

The assessment of outcomes encompasses the following domains: low back pain intensity, somatic dysfunction, pain-related fear and avoidance behaviors, health status, and cerebral cortex activation characteristics. Assessments will be performed at baseline, mid-intervention (week 4), post-intervention (week 8), and follow-up (week 16). It is worth mentioning that participants will be required to rate the overall efficacy of the received intervention using the Global Perceived Effect (GPE), at week 8 (post-intervention). Additionally, functional near-infrared spectroscopy (fNIRS) will be employed by the researchers to assess cerebral cortex activation characteristics in each group at baseline and week 8 (end of intervention).

#### 2.7.1 Primary outcome

##### 2.7.1.1 Numeric Rating Scale (NRS)

This instrument serves as a standardized tool for assessing lumbar pain intensity, utilizing a numerical rating system spanning from 0 (indicating complete absence of pain) to 10 (representing the maximum tolerable pain threshold) (11). For patients with chronic LBP, a 2-point difference on the NRS was defined as the minimal clinically important difference (MCID) (25). The NRS score at week 8 will be regarded as the primary outcome measure.

#### 2.7.2 Secondary outcomes

##### 2.7.2.1 Oswestry Disability Index (ODI)

This questionnaire is designed to evaluate functional limitations caused by low back pain across ten domains (26). Each domain provides six response options scored from 0 to 5, where 0 indicates minimal or no disability and 5 indicates the most severe disability. Higher scores indicate greater disability. An MCID greater than 10 points is considered clinically significant for ODI (27).

